### 13.1.1 Power Calculations

We will send invitations to 1280 potential participants from 64 GP practices with the aim of recruiting 640 for further testing. 250 of the screened participants will then be randomised. In addition, suitable participants from outpatient clinics run by [name] and [name] will also be invited to take part.

Our primary outcome will be based on a 'gold' standard test of exercise tolerance defined by peak  $\text{VO}_2$  using CPET and assessed at baseline and after the treatment with the trial drug. We hypothesise that the spironolactone will improve peak  $\text{VO}_2$  compared to the placebo treated subjects. We base our power calculation for peak  $\text{VO}_2$  on the published values of peak  $\text{VO}_2$  in subjects with HFpEF ( $16 \pm 5$  ml/min/kg). We anticipate a difference of 2ml/min/kg in the improvement in peak  $\text{VO}_2$  after 2-year treatment with spironolactone compared with the control group. Unfortunately this publication does not give a standard deviation on the change in peak  $\text{VO}_2$  from baseline but a similar trial, Edelmann et al provides that statistic (5 ml/min/kg) and also reports a similar magnitude of effect.

A sample size of 100 patients in each group will have 80% power to detect a difference in means of 2.000 assuming that the common standard deviation is 5.000 (effect size =0.40) using a two group t-test with a 0.05 two-sided significance level. Sample size calculation was conducted using the nQuery software. Approximately, for 80% power at 5% significance, sample size in each group would be  $15.68/(\text{effect size})^2$ . To accommodate a loss to follow-up of 20% of patients from each group would imply initially recruiting a total sample size of 250 ( $250 \times 0.8 = 200$ ) in order to still retain 200 patients in all. Loss of 20% of patients would still enable effects in excess of 2.3ml/min/kg (effect size=0.46) to be detected with 90% power at the 5% significance level. Sample size= $21.0/(\text{effect size})^2$  for 90% power, 5% significance. At the other extreme zero loss to follow up from 250 patients would lead to 88% power to detect a 2 ml/min/kg at 5% significance Prediction of 20% loss to follow up is based on a 10% loss per year and composed of 5% due to death and 5% due to other reasons. The relevant population of patients would be under regular follow up and as such would have relatively lower expected mortality.

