## APPENDIX 1. Mechanistic substudy

### Clinical utility of biomarkers of fibrosis and hemostasis in chronic atrial fibrillation: A substudy of the IMPRESS-AF trial

#### Abstract:

Experimental data suggest role of cardiac fibrosis and hemostasis in cardiac stiffening and development of heart failure with preserved ejection fraction in atrial fibrillation (AF). However, limited data exist on clinical utility of blood markers of fibrosis and hemostasis in chronic AF with adequate oral anticoagulation for stroke prevention. The proposed study aims to establish potential of blood markers of fibrosis and hemostasis as predictors of deterioration of exercise tolerance, quality of life, diastolic function and rates of hospital admissions in patients with chronic AF and preserved left ventricular ejection fraction; to determine utility of the fibrotic and hemostatic biomarkers to predict capacity of aldosterone inhibitor, spironolactone to prevent deterioration of exercise tolerance, quality of life, diastolic function and prevent hospital admissions in these patients.

The double-blinded randomised IMPROVED exercise tolerance In heart failure With PRESERVED Ejection fraction by Spironolactone On myocardial fibrosis In Atrial Fibrillation (IMPRESS-AF) trial awarded by NIHR-EME program will assess impact of 2-year treatment with an aldosterone antagonist, spironolactone vs placebo in 250 AF patients with preserved cardiac contractility. The trial will establish impact of spironolactone on exercise tolerance, quality of life, left ventricular diastolic function, and rates of hospitalisations. We propose to use population of the IMPRESS-AF patients to address the aims above using the blood tests from those patients.

**Aims of the substudy:** (i) To establish utility of blood markers of fibrosis and hemostasis as predictors of deterioration of exercise tolerance, quality of life, diastolic function and rates of hospital admissions in patients with chronic atrial fibrillation (AF) and preserved left ventricular (LV) ejection fraction (EF); (ii) to determine utility of the fibrotic and hemostatic biomarkers to predict capacity of aldosterone inhibitor, spironolactone to prevent deterioration of exercise tolerance, quality of life, diastolic function and prevent hospital admissions in these patients.

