#### Original hypotheses of the proposed study:

We hypothesise that in patients with permanent AF with preserved LVEF (on standard oral anticoagulant therapy) high systemic levels of biomarkers of fibrosis and procoagulant values of hemostatic parameters can be used as predictors of deterioration of exercise tolerance, quality of life, diastolic function, hospital admission and predictors of higher clinical efficacy of treatment with spironolactone.

**Background:** The prevalence of AF was 4.7% in general practice in people aged 65 years or more. A third of AF patients suffer symptomatic HF, of which most have HFpEF. In patients with HFpEF, AF is present in about 40% and is independently associated with an increased risk of death and hospitalisation with HF. Data from the CHARM program, which studied 7,599 patients with symptomatic HF, demonstrated that AF was associated with increased risk of the death or hospitalisation for worsening HFpEF.

Activation of profibrotic pathways, increased production of myocardial collagen lead to increased pressure load in the heart, diastolic dysfunction and increased cardiac stiffness. This process is linked to an increased myocardial collagen turnover and shift in the balance between matrix metalloproteinases (MMP) and their inhibitors in favour of excessive myocardial fibrosis. Published evidence from AF populations supports a central role of atrial fibrosis in electrical and structural atrial

|                          |            |               |            |       |          |
|--------------------------|------------|---------------|------------|-------|----------|
| Trial name:              | IMPRESS-AF |               |            |       |          |
| Protocol version number: | 6.0        | version date: | 12/10/2015 | Page: | 62 of 67 |

remodelling, and an independent predictive value for the high risk of cerebrovascular events. We have previously demonstrated that presence of AF and its progression from paroxysmal to chronic form are associated with incremental increase in left ventricular fibrosis, which significantly correlated with deterioration in parameters of diastolic function.

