**Sample size – calculations:** The sample size has been originally calculated to provide sufficient power to assess impact of the spironolactone treatment for the outcomes of the IMPRESS-AF trial and it will provide statistical power sufficient to assess utility of the fibrotic parameters to predict the study outcomes and efficacy of treatment with spironolactone (with more 80% power) using appropriate regression analysis (linear regression and Cox regression). Further exploratory analyses will incorporate interaction terms between intervention/control and each of the covariates, including parameters of fibrosis. Backward elimination will be used to remove non-significant interactions and then non-significant main effects.

Regarding the nitrite/platelet part of the study we aim to obtain pilot data for a future bigger and specifically designed study. Based on our previous studies it is estimated that n=20 AF patients will be necessary for the evaluation of plasma nitrite concentrations. For platelet aggregation studies, previous studies utilised n=14 HF patients for the determination of the effect of GTN in whole blood. Based on the above, we estimate that n=40 HF patients will be sufficient to determine the effects of nitrite on aggregation and at molecular level in isolated platelets in comparison to healthy controls (n=20 for platelet aggregation, n=20 for western blot).

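### Appendix 1 claims more than 80% power for markers to predict spironolactone efficacy, but the sample was sized only for main effects; for peak VO2 the figure is not met at an interaction as large as the planned effect

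*Protocol*

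**What the plan says.** Appendix 1, under the sample-size heading, makes no calculation of its own for the fibrotic markers. It starts from the main trial: "The sample size has been originally calculated to provide sufficient power to assess impact of the spironolactone treatment for the outcomes of the IMPRESS-AF trial". It then says of the same sample that "it will provide statistical power sufficient to assess utility of the fibrotic parameters to predict the study outcomes and efficacy of treatment with spironolactone", and continues "with more 80% power) using appropriate regression analysis (linear regression and Cox regression". The power figure therefore covers two questions: whether markers predict outcomes, and whether they predict the efficacy of spironolactone.

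The second question is a stated aim. Aim (ii) is "to determine utility of the fibrotic and hemostatic biomarkers to predict capacity of aldosterone inhibitor, spironolactone to prevent deterioration of exercise tolerance", and likewise for quality of life, diastolic function and admissions. The substudy hypothesis is that high marker levels are "predictors of higher clinical efficacy of treatment with spironolactone".

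The next sentence of the sample-size paragraph reads "Further exploratory analyses will incorporate interaction terms between intervention/control and each of the covariates, including parameters of fibrosis". Non-significant interactions are then removed by backward elimination.

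The calculation relied on is in section 13.1.1: "We anticipate a difference of 2ml/min/kg in the improvement in peak" VO2, with SD 5. The result is "A sample size of 100 patients in each group will have 80% power to detect a difference in means of 2.000".

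**The concern.** A marker that predicts efficacy is one across whose levels the treatment effect differs. In a regression that is the marker-by-treatment interaction, not the treatment effect and not the marker's own association with outcome. Section 13.1.1 sizes only differences between arms. An interaction is estimated less precisely than a main effect from the same patients: with a 50:50 marker split its standard error is exactly twice as large. A power figure of about 80% for a main effect of 2 ml/min/kg therefore cannot be carried over to an interaction of that size.

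At stake is how a null result is read. If the protocol says the predictive question had more than 80% power, a non-significant interaction invites the conclusion that the markers do not identify patients who benefit more. With lower power that conclusion would not be justified. Where several markers are tested and only significant terms are kept, the surviving estimates will also tend to be too large.

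**Working it through.** **Inputs from section 13.1.1.** 100 evaluable per arm (N = 200), or 125 per arm (N = 250) with no loss; two-sided 5% significance (z = 1.96). Planned differences and SDs of change: peak VO2 2 and 5; 6-minute walk 26 and 48; E/e' 3.2 (absolute value) and 2.08; MLWHF 5 and 11.35. Allocation is 1:1 (section 6.2).

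**Assumptions, because the protocol gives no figure.** The interaction is as large as the planned main effect. The marker is either split 50:50 or is continuous, normal and linear in its effect on the treatment difference.

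**1. The plan's own figure.** Main-effect SE = 5 × √(2/100) = 0.707. Power = Φ(2/0.707 − 1.96) = 80.7% (t-test 80.4%). With 125 per arm it is 88.5% (t-test 88.3%). The stated 80% and 88% reproduce.

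**2. Interaction for peak VO2, marker split 50:50.** There are four cells of N/4, so SE = SD × √(16/N).
- N = 200: SE = 5 × √(16/200) = 1.414; power = Φ(2/1.414 − 1.96) = 29.3%.
- N = 250: SE = 1.265; power = 35.3%.
- With N = 200, an interaction of 1 has 11% power, 3 has 56% and 4 has 81%.
- With only 25% to 33% of patients marker-high, an interaction of 2 has 23% to 26% power (N = 200) or 28% to 32% (N = 250).

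**3. Interaction for peak VO2, continuous marker.** SE per marker SD = SD × √(4/N), which is 0.707 at N = 200 and 0.632 at N = 250. The means of the two halves of a normal marker lie 2 × √(2/π) = 1.596 SD apart. A difference of 2 between halves is therefore a slope of 2/1.596 = 1.25 per SD.
- N = 200: Φ(1.25/0.707 − 1.96) ≈ 43%.
- N = 250: Φ(1.25/0.632 − 1.96) ≈ 51%.

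**4. What 80% power needs.** The detectable interaction is (1.96 + 0.84) × SE. At N = 200 this is 3.96 ml/min/kg between median halves of a dichotomised marker, or 1.98 ml/min/kg per SD of a continuous one. At N = 250 it is 3.54 or 1.77. For an interaction of 2 with a 50:50 split, N = 16 × 25 × 7.85/4 ≈ 785.

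**5. Other continuous outcomes, 50:50 split, N = 200.** The interaction equals the planned difference, and √(16/200) = 0.2828.

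| Outcome | Interaction | SE | Ratio | Power |
|---|---|---|---|---|
| 6-minute walk | 26 | 48 × 0.2828 = 13.58 | 1.92 | 48% |
| MLWHF | 5 | 11.35 × 0.2828 = 3.21 | 1.56 | 34% |
| E/e' | 3.2 | 2.08 × 0.2828 = 0.588 | 5.44 | over 99% |

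An E/e' interaction of half the planned difference (1.6) has 78% power, or 86% at N = 250.

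**6. Prognostic aim (i).** The correlation detectable with 80% power is tanh[(1.96 + 0.84)/√(N − 3)], which is 0.20 at N = 200 and 0.18 at N = 250.

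**7. Cox regression.** Appendix 1 gives no event count, so its power cannot be checked.

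**The case against.** The strongest defence is that the interaction terms are labelled exploratory in the very next sentence, and also in section 13.1, so the protocol does not present them as confirmatory. That is true and lowers the weight of the point. It does not undo the sentence before it, which attaches more than 80% power to predicting efficacy itself. In a regression that question is answered only by the interaction.

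A second objection is that 29% is not a property of the trial. The 2 ml/min/kg is a planned main effect, no interaction size is planned, and nothing in the protocol calls for a median split. This stands. The 29% must be quoted with both assumptions and beside the continuous-marker figures, which are clearly higher.

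A third is that peak VO2 is only one of several outcomes in aim (ii). This also stands: with the protocol's own inputs for E/e', an interaction as large as the planned difference is very well powered.

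A reader might also infer that backward elimination is bound to discard real interactions. The figures do not support that. If removal is at the 5% level, a true interaction of 2 ml/min/kg with a 50:50 split at N = 200 would be non-significant about 71% of the time (100 − 29), but one of 4 only about 19% (100 − 81). Elimination within an analysis labelled exploratory is a matter of preference, provided the removed estimates are reported.

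**Conclusion.** The point holds in a limited form. The statement of more than 80% power is unsupported for aim (ii). For peak VO2, the trial's primary outcome, it is not met at an interaction equal to the planned main effect: about 29% to 35% with a 50:50 split and 43% to 51% with a continuous normal marker, for 200 to 250 patients. An interaction of that size is already generous, since it means, for example, a benefit of 3 in one half and 1 in the other. Reaching 80% at N = 200 takes about 4 ml/min/kg between median halves, or about 2 ml/min/kg per marker SD. These figures rest on the protocol's SD of 5, one marker tested at the 5% level and complete samples; missing samples or correction for several markers would lower them.

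A reader might infer that the whole substudy is underpowered. The protocol does not support that. Aim (i) is plausibly powered, E/e' differs sharply from the other outcomes, and the Cox analyses cannot be judged either way. The main trial's power figures reproduce, and neither its sample size nor its primary analysis is affected. Severity is minor.

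**What to change.** Three changes to the wording of Appendix 1:

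1. Limit the statement of more than 80% power to the prognostic aim (i), and state the association it refers to: a correlation of about 0.20 with 200 patients.
2. Describe aim (ii) as exploratory and state the detectable interaction per outcome, with its assumptions and in the form that will be fitted. For a continuous marker, N = 200, 80% power and two-sided 5% significance, this is 2.80 × SD × √(4/200) = 0.396 × SD per marker SD: about 2.0 ml/min/kg for peak VO2 (SD 5), 19 m for 6-minute walk (SD 48), 0.82 for E/e' (SD 2.08) and 4.5 points for MLWHF (SD 11.35). Median-split figures should not stand beside a continuous-marker model. For the Cox analyses, give the expected number of events or make no power claim.
3. Report every marker-by-treatment estimate with its confidence interval, including those removed by backward elimination.

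The cost is wording and a fuller results table. The stated power becomes less favourable. No change to recruitment, data collection or the primary analysis is needed.
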